## Abstract

**Background:**

Cytotoxic treatments such as chemo- and radiotherapy and immune therapies are required in cancer diseases. These therapies have the potential to cure patients but may also have an impact on gonadal function and, therefore, on fertility. Consequently, fertility preservation treatments such as freezing of gametes and gonadal tissue might be required. However, as detailed data about the necessity to perform fertility preservation treatment are very limited, this study was designed to fill this data gap.

**Objective:**

Primary objective of this study is to analyze the impact of cancer therapies and chemotherapies on the ovarian reserve and sperm quality. Secondary objectives are to analyze the (1) impact of cancer therapies and chemotherapies on other fertility parameters and (2) probability of undergoing fertility preservation treatments in relation to specific cancer diseases and treatment protocols and the probability to use the frozen gametes and gonadal tissue to achieve pregnancies.

**Methods:**

First, previously published studies on the gonadotoxicity of chemo- and radiotherapies among patients with cancer will be systematically analyzed. Second, a prospective cohort study set up by approximately 70 centers in Germany, Switzerland, and Austria will collect the following data: ovarian function by analyzing anti-Müllerian hormone (AMH) concentrations and testicular function by analyzing sperm parameters and total testosterone immediately before and around 1 year after gonadotoxic therapies (short-term fertility). A follow-up of these fertility parameters, including history of conceptions, will be performed 5 and 10 years after gonadotoxic therapies (long-term fertility). Additionally, the proportion of patients undergoing fertility-preserving procedures, their satisfaction with these procedures, and the amount of gametes and gonadal tissue and the children achieved by using the frozen material will be analyzed. Third, the data will be merged to create the internet-based data platform FertiTOX. The platform will be structured in accordance with the *ICD* (*International Classification of Diseases*) classification of cancer diseases and will be easily be accessible using a specific App.

**Results:**

Several funding bodies have funded this study. Ten systematic reviews are in progress and the first one has been accepted for publication. All Swiss and many German and Austrian ethics committees have provided their approval for the prospective cohort study. The study registry has been set up, and a study website has been created. In total, 50 infertility centers have already been prepared for data collection, which started on December 1, 2023.

**Conclusions:**

The study can be expected to bridge the data gap regarding the gonadotoxicity of cancer therapies to better counsel patients about their infertility risk and their need to undergo fertility preservation procedures. Initial data are expected to be uploaded on the FertiTOX platform in 2026.

**Trial Registration:**

ClinicalTrials.gov NCT05885048; https://clinicaltrials.gov/study/NCT05885048

**International Registered Report Identifier (IRRID):**

DERR1-10.2196/51145

## Introduction

### Background

After reaching milestones in fertility preservation such as freezing of sperm and testicular tissue—and more recently, the first birth after transplantation of cryopreserved ovarian tissue [1], the introduction of luteal-phase random-start gonadotropin stimulation [2], and vitrification of oocytes [3]—fertility preservation treatments have been introduced in most countries, and fertility preservation has been accepted and defined as an important element to be considered before cancer treatments (Figure 1).

Medically, this has been evidenced by several national and international guidelines stating that fertility preservation counseling is required before administering gonadotoxic therapies [4-11], and this has been politically been shown as many countries have introduced reimbursement or coverage of fertility preservation treatments.

However, data about the gonadotoxicity of the numerous cancer treatment regimens are mostly very limited. Additionally, a recent study in mice has revealed that immune therapies such as checkpoint inhibitors have substantial impact on the ovarian reserve [12], but human data are not yet available.

Accordingly, indications for or against fertility-preserving therapies are not well defined with either the risk of overtreating patients or imposing unnecessary medical risks and burdens to the patients and, therefore, unnecessarily postponing the gonadotoxic therapies. However, the risk of undertreating patients with respective therapies imposes the risk of infertility, which can have a substantial impact on their quality of life after the onset of cancer [13].

Meanwhile, effective methods are available to reliably quantify the gonadotoxicity of cancer therapies. In women, ovarian function can be evaluated by analyzing anti-Müllerian hormone (AMH), follicle-stimulating hormone (FSH), luteinizing hormone (LH), and estradiol (E2) concentrations, and in men, testicular function is evaluated by analyzing sperm counts and total testosterone, FSH, and LH concentrations.

**Figure 1 figure1:**
[figure not shown]
Algorithm for indicating fertility preserving therapies in women and men.

Even though these functional parameters exist, prospective and systematic short- and long-term data regarding the impact of specific cancer therapies on fertility based on these parameters are limited. It can be assumed that this is due to a lack of effective fertility preservation network structures in most countries. However, in Switzerland, Germany, and Austria, network structures that permit a systematic and continuous large-scale data analysis have been established.

Data should be made available as an easily accessible internet-based platform that is merged with already published data on the gonadotoxicity of cancer therapies and other relevant data such as the 5-year survival rates of the cancer diseases. The data platform will support physicians and other experts as well as patients in counseling about fertility risks imposed by cancer treatments and the necessity to undergo fertility-preserving measures.

We, therefore, designed a study to collect data on the gonadotoxicity of cancer therapies by systematically analyzing already published data and by setting up an international multicenter prospective cohort study to collect data on the gonadotoxicity of chemotherapies, radiotherapies, and immune therapies among men and women and to upload summarized data on an internet-based data platform.

### Objectives

The primary objective is to determine whether cancer therapies and specific chemotherapy protocols reduce AMH concentrations in women and sperm quality in men.

Secondary objectives are to analyze the impact of cancer therapies and chemotherapies on other fertility parameters such as the probability of undergoing fertility-preserving treatments in relation to the type of cancer disease and specific treatment protocols, the number of children, the future wish to have children, and age. Further objectives are to assess satisfaction with the decision to have undergone fertility-preserving procedures, the proportion of women and men who use their frozen gametes to achieve a pregnancy, the effect of different gonadotoxic therapies on long-term fertility, and the quality of life after the administration of cancer therapies. 

## Methods

### Study Design

The study consists of 2 parts: first, a series of systematic reviews; second, an international multicenter prospective exploratory observational cohort study of fertility-related parameters with a long-term follow-up of the fertility of patients with cancer in university and nonuniversity public hospitals and private infertility centers in Germany, Switzerland, and Austria. All data will be uploaded on an internet-based data platform.

### First Part: Retrospective Systematic Data Analysis

A series of systematic reviews will be performed in Switzerland, one of which will be performed in Germany. The reviews encompass diseases for which a sufficient number of studies has been published to perform a systematic review and which are relevant regarding fertility and fertility-preserving issues. The following reviews were initiated in 2023 and 2024 or are expected to be published in 2024 and 2025. They are registered in PROSPERO:

A systematic review of the gonadotoxicity of Osteoscarcoma and Ewing´s sarcoma chemotherapies in postpubertal females and males: CRD42023331654, accepted for publication (*Journal of Adolescent and Young Adult Oncology*).Effects of chemotherapy and radiation in male genital organ tumors on ovarian and testicular function and fertility: CRD42023384057, submitted for publication in 2024.Effects of chemotherapy and radiation in mesothelial and soft tissue cancer on ovarian and testicular function and fertility: CRD42023385402, to be submitted for publication in 2024.Effects of chemotherapy, radiation and immunotherapy in breast cancer on ovarian and testicular function and fertility: CRD42023384042, to be submitted for publication in 2024.Effects of bone marrow transplantation in hematological cancers on ovarian and testicular function and fertility: CRD42023486928, to be submitted for publication in 2024.Effects of chemotherapy and radiation in eye, brain and central nervous system cancer on ovarian and testicular function and fertility: CRD42023385408, to be submitted for publication in 2024.Effects of chemotherapy and radiation in Hodgkin lymphoma on ovarian and testicular function and fertility: CRD42023384052, to be submitted for publication in 2025.Effects of chemotherapy and radiation in Non-Hodgkin lymphoma on ovarian and testicular function and fertility: CRD42024511940, to be submitted for publication in 2025.Effects of chemotherapy and radiation in colorectal cancer on ovarian and testicular function and fertility: CRD42024511944, to be submitted for publication in 2025.Effects of chemotherapy and radiation in leukemia on ovarian and testicular function and fertility: CRD42024511946, to be submitted for publication in 2025.

### Second Part: Prospective Cohort Study

The cohort study will collect data on the ovarian reserve and sperm from patients undergoing gonadotoxic therapies. Data collection was initiated on December 1, 2023, and will be continued at least for 5 years to analyze short-term fertility. Long-term fertility data will be collected until at least 2036. An initial version of the FertiTOX internet-based platform is expected to be set up in 2026. The trial is registered in ClinicalTrials.gov (NCT05885048).

### Inclusion Criteria

Each center that counsels patients with cancer about fertility issues and can also provide fertility-associated parameters may participate. A prerequisite requirement is that each center has received ethical approval for the study. Even though the study is intended to mainly include FertiPROTEKT network centers [14] and FERTISAVE [15] networks in Germany, Switzerland, and Austria, any other center worldwide can participate if the inclusion criteria are fulfilled.

Women and men aged 14-50 years (18-50 years in Germany due to national regulations) undergoing cancer therapies using chemotherapy, radiotherapy, or immune therapy (Figure 1) will be included.

### Recruitment and Informed Consent Procedure

Patients are recruited by reproductive physicians who are associated with the participating infertility centers. Approximately 70 centers (44 in Germany, 21 in Switzerland, and 6 in Austria) will participate in the study and will collect data (see Multimedia Appendix 1).

Patients who need gonadotoxic therapies will be counseled before the onset of the respective therapies. During counseling, patients are screened for their eligibility to be included in the study.

Furthermore, patients will be provided counseling forms to provide informed consent before the onset of gonadotoxic therapy to collect specific basic data and data on gonadal function from patients with cancer. Data will also be collected 12-15 months and 5 and 10 years after the end of gonadotoxic therapy.

The study participants will be informed that they will be contacted by the fertility center or a defined coworker of the study by telephone, email, or post to collect the respective data after the administration of gonadotoxic therapy.

### Study Registry

Data will be collected using the REDCap (Research Electronic Data Capture) software, a secure web application for building databases [16]. The REDCap registry has been set up and optimized by the study consortium with the support of the Clinical Trials Unit in Bern, REDCap technicians, and statisticians. The contents of the study registry (consultation before and 12-15 months after the end of the gonadotoxic therapy) are shown in the paper version of the registry (Multimedia Appendices 2-5). The participating centers will add the data to the registry without adding any definite identifiers such as name and date of birth. The participating centers can only see their patients. Patients can be traced with an individual code that is safeguarded by the centers. Only very few authorized persons will be provided access to all data in order to assess the data quality and to remind the centers to invite the patients for follow-up consultations.

### End Points

The primary end points are the AMH concentration in women and sperm count before and after gonadotoxic treatments. End points will be assessed before and 12-15 months after the end of the gonadotoxic treatments (patients with melanoma receiving adjuvant checkpoint inhibitor treatment will be evaluated every 3 months).

Secondary end points are FSH, LH, and E2 concentrations in women and total testosterone, FSH, and LH concentrations, total sperm count, and sperm motility in men. Further secondary outcome parameters are the number of patients who freeze gametes and gonadal tissue and satisfaction with the decision to have undergone fertility-preserving measures.

Long-term end points to be determined 5 and 10 years after the end of the gonadotoxic therapy are the abovementioned hormone and sperm parameters as well as the number of patients who become pregnant after gonadotoxic therapies spontaneously or after the use of frozen gametes and gonadal tissue.

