### Data Analysis

The impact of cancer therapies and chemotherapies on the primary outcomes will be assessed for each *ICD* cancer group [19] and for each specific treatment regimen separately by comparing values measured before and after the gonadotoxic therapy using paired *t* tests. *P* values will be adjusted for multiple testing using the false discovery rate controlling procedure.

Consequences on other fertility parameters measured before and 12-15 months after the end of gonadotoxic therapy (ie, AMH, FSH, LH, and E2 concentrations in women and total testosterone, FSH, and LH concentrations and total sperm count, sperm concentration and motility in men) will be assessed using the same methodology, but without false discovery rate adjustment. Long-term consequences will be investigated later by comparing values measured before and 5 and 10 years after the gonadotoxic therapy. However, due to the long period until the final analysis, statistics might be adapted in relation to future development of cancer and fertility-preserving therapies.

As age was identified to potentially modify the effect of gonadotoxic therapy on female fertility, we will additionally conduct stratified analyses and document the impact of gonadotoxic therapy in the different female age groups.

Finally, the effects of different cancers, treatment protocols, age, and the presence of the patients’ children before cancer therapy on primary and secondary fertility outcomes will be analyzed using linear mixed effect models.

The frequency of patients undergoing fertility-preserving treatments, namely freezing of ovarian tissue, oocytes and embryos, testicular tissue, and sperm will be calculated for each *ICD* cancer group and for each specific treatment protocol separately and additionally presented with the associated 95% Wilson CI. Potential effects of the patients’ characteristics on the abovementioned binary outcomes will be analyzed using logistic regression analysis.

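### The before-after comparison of FSH, LH, E2 and testosterone takes no account of hormone treatment, contraception or pregnancy at sampling, so drug-set values are credited to the cancer regimen.

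*Protocol article*

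**What the plan says.** All references are to the Methods of the protocol article.

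- **End Points** lists the secondary hormones: "Secondary end points are FSH, LH, and E2 concentrations in women and total testosterone, FSH, and LH concentrations". On timing: "End points will be assessed before and 12-15 months after the end of the gonadotoxic treatments".
- **Inclusion Criteria** defines the exposure. Patients enter if they are "undergoing cancer therapies using chemotherapy, radiotherapy, or immune therapy". Endocrine therapy is not named.
- **Data Analysis** tests the primary outcomes "by comparing values measured before and after the gonadotoxic therapy using paired" *t* tests, by ICD group and by regimen. The other fertility parameters "will be assessed using the same methodology, but without false discovery rate adjustment".
- **Data Analysis** names two refinements. Stratified analyses will "document the impact of gonadotoxic therapy in the different female age groups", and linear mixed models will examine "the effects of different cancers, treatment protocols, age, and the presence of the patients’ children before cancer therapy".
- **End Points** adds for the long term: "Long-term end points to be determined 5 and 10 years after the end of the gonadotoxic therapy are the abovementioned hormone and sperm parameters". The same sentence counts pregnancies, including those after use of frozen gonadal tissue.

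**The concern.** FSH, LH, E2 and testosterone indicate gonadal function only if nothing else sets them when the sample is taken. At 12-15 months some women may be on estrogen replacement, ovarian suppression or hormonal contraception, or may be pregnant. Some men may be on testosterone. The follow-up clock starts at the end of gonadotoxic treatment, and nothing in the text delays sampling until an endocrine treatment has ended.

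The within-patient tests have no untreated comparator, so the whole before-after difference is attributed to the regimen. Replacement is also linked to the outcome: patients whose gonads have failed are the ones likely to receive it. The most toxic regimens can therefore lose the most signal. The results are meant for counselling on infertility risk, and the Introduction of the article names both overtreatment and undertreatment as harms.

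**Working it through.** The plan states no figure on this point. The check is therefore a reading of the text, followed by illustrations whose assumptions are marked.

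**1. Reading.** Set side by side, the exposure is chemotherapy, radiotherapy or immune therapy; the clock runs from its end; the test is a paired difference; and the named adjusters are female age group, cancer, protocol, age and prior children. None of these describes the hormonal state at sampling.

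**2. Direction.** Replacement moves the replaced hormone, and with it FSH and LH, back towards baseline, which hides failure. Central suppression lowers E2 and testosterone, as failure does. It also lowers FSH and LH, which primary failure raises. The direction of bias therefore depends on the hormone and the drug.

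**3. Dilution by replacement (assumed values).** Let p be the share of patients with failure, h the share of those on replacement that cancels the shift, and D the shift under failure.

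- True mean change: pD
- Unrestricted comparison: p(1−h)D
- Comparison in untreated pairs only: p(1−h)D/(1−ph)

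With p = 0.3:

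| h | True | Unrestricted | Untreated pairs only |
|---|---|---|---|
| 0.25 | 0.30D | 0.225D | 0.225D/0.925 = 0.243D |
| 0.50 | 0.30D | 0.15D | 0.15D/0.85 = 0.176D |
| 0.75 | 0.30D | 0.075D | 0.075D/0.775 = 0.097D |

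The unrestricted change is too small by the fraction h. Restriction alone recovers little: at h = 0.5 it regains 0.026D of the 0.15D lost, about 18%.

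**4. Effect on power (assumed values).** For a paired *t* test, dz = d/√(2(1−ρ)), with noncentrality dz·√n. With ρ = 0.5, dz = d. As a check of the formula, female genital organs in Table 1 (350/3, n = 116, d = 0.5, alpha 0.0006) gives 96.5%, as printed.

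For a secondary hormone, take alpha 0.05 (no adjustment is planned), d = 0.5 and ρ = 0.5. The article sets ρ for AMH and sperm only, so its use here is an assumption. Take n = 33 women per protocol, from mesothelial and soft tissue: 200/3/2. If a share q of all patients shows no shift because of treatment, the mean shift is 0.5(1−q):

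| q | Shift | Power |
|---|---|---|
| 0 | 0.50 | 79.5% |
| 10% | 0.45 | 70.8% |
| 25% | 0.375 | 55.1% |
| 50% | 0.25 | 28.5% |

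**5. Spurious effects in a large group (assumed values).** Breast has 2000/6 = 333 patients per protocol. A treatment-induced shift of 0.2 SD in a secondary hormone, with no gonadal damage, gives noncentrality 0.2 × √333 = 3.65 and is significant at 0.05 in 95% of studies. A large sample makes such an artefact easier to detect; it does not remove it.

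**6. AMH, conditional only.** If 30-60% of women were on a suppressing treatment at follow-up but not at baseline, and if it lowered AMH by 20-50%, a regimen without ovarian toxicity would show a fall of 0.3 × 0.2 = 6% to 0.6 × 0.5 = 30%. The documents support neither range.

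**The case against.** The strongest reply is that this rests on silence in a condensed article. Which samples are evaluable under concomitant hormones may be settled in the full protocol or analysis plan, and the registry forms in Multimedia Appendices 2-5, which are not shown, may already record these states. That stands in part. A reader might infer that the sponsor chose to compare values whatever the hormonal state, or that the registry omits the item. The documents support neither. The article does, however, specify the comparison and its refinements, and recording a state does not by itself change the stated test.

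Other tempting readings also go too far:

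- *Suppression mimics gonadal failure.* This could hold for E2 or testosterone. It fails for FSH and LH, which make up four of the six secondary hormone end points.
- *The primary AMH result is biased.* No document figure supports this. It is an assumption to be tested.
- *A functioning graft will be counted as preserved ovarian function.* The article does not say so. It mentions pregnancy and use of frozen tissue only with the 5- and 10-year end points, for which Data Analysis says the statistics may be adapted.

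A further objection is that restricting to untreated pairs discards the most damaged patients. Step 3 of the working confirms this, so restriction cannot stand alone. Finally, the study is exploratory and these end points are secondary, which limits the weight of the point.

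**Conclusion.** The concern holds for the 12-15-month comparison of FSH, LH, E2 and total testosterone. Run as written, it attributes to the regimen hormone values that are supplied or suppressed by another treatment, or altered by pregnancy. Replacement biases towards apparent safety. Suppression acts in a direction that differs by hormone.

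The size cannot be determined from the documents. A loss of 25% to 75% of the failure-related change follows only from the assumed h of 0.25 to 0.75 and from replacement fully cancelling the shift. The power figures also assume an unchanged SD and a correlation of 0.5. For AMH and sperm count the point supports a sensitivity analysis and no more. For 5 and 10 years it is a matter to settle when that analysis is specified.

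**What to change.** In Data Analysis:

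1. Make the FSH, LH, E2 and testosterone before-after comparison in pairs where neither sample was taken under sex hormone treatment, ovarian suppression, hormonal contraception or in pregnancy. Show the remaining pairs separately.
2. Beside it, over all followed patients, report the proportion on replacement for gonadal failure as an adverse gonadal outcome. Without this, the restricted comparison still understates harm.
3. Keep the primary AMH and sperm count analyses as planned, and repeat them in the restricted set as a sensitivity analysis. The same selection problem applies there, so read the two results together.
4. When the 5- and 10-year analysis is specified, present hormone values taken in pregnancy or after transplantation of gonadal tissue separately.

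Use the registry's existing items if Appendices 2-5 already record these states; otherwise add one item per sample. Clinical management does not change. The cost is analysis wording and fewer pairs for the hormone end points, mainly in breast cancer.
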